Randomization will be performed centrally by a consultant at the SAS Institute A/S (Copenhagen, Denmark). The allocation sequences will be computer-generated with varying block size, and will be kept unknown to the investigators. Randomization will be stratified by clinical trial site and LT4 treatment duration (<3 months or ≥3 months) and the allocation ratio of intervention and control will be 1:1.

#### **
*Informed consent procedure*
**

Potential participants include all patients with suspected AIT who receive LT4 and are identified at referral or visits to the outpatient clinics or via advertising, as previously described. When AIT is confirmed (serum TPO-Ab ≥ 100 IU/ml, measured within the last 12 months), the patient is invited to an information visit. This visit involves obtaining medical history and written informed consent, blood and urine sampling, and information about trial contact as well as randomization.

#### **
*Concomitant medication or treatment*
**

The trial interventions are given in addition to conventional LT4 treatment. Treatment of the hypothyroidism *per se* will take place at participating clinical trial sites, with LT4 treatment at all clinical trial sites aiming for a serum TSH level within reference ranges, as recommended in local clinical guidelines. Patients are normally followed with blood sampling every 1 to 3 months to adjust LT4 dosage according to TSH levels, as well as visits in the outpatient clinic every 3 to 6 months. Participants in the CATALYST trial will be followed with blood sampling during the trial period, as stated in local clinical guidelines. Participants are advised not to take selenium supplementation in addition to the intervention. A dose of selenium common in multivitamin tablets is, however, allowed and participants are instructed and informed about this upon trial entry, and in the written participant information. The participants’ consumption of additional selenium supplements will be monitored during the trial at specific time points.

#### **
*Monitoring participant adherence to intervention*
**

During the trial, participants self-report their adherence to the intervention at the trial visits (3 months and 12 months after randomization) by stating the number of days a week they take their tablets. Participants will also be instructed to bring remaining tablets and empty containers to the 12 month visit, where they will be counted and registered by an investigator or trial nurse.

#### **

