### Statistical analyses

#### **
*Primary outcome: sample size estimation*
**

The primary outcome is thyroid-related quality of life during 12 months’ intervention, as measured by a composite score from the ThyPRO questionnaire. Sample size estimation is based on this outcome.

The trial should be sufficiently powered to identify a difference between the intervention and the control group of four points on the 0 to 100 ThyPRO composite scale, corresponding to a small to moderate effect. In previously obtained data, the standard deviation of ThyPRO-scores (sigma level) was 20 points [14]. With a correlation between observations on the same participant of 0.50, and a power of 80% and a type I error probability (two-sided α level) of 0.05, a sample size of 236 experimental participants and 236 control participants is required. The sample size estimate is based on a design with five repeated measurements having a compound symmetry covariance structure [51].

#### **
*Secondary outcomes: power estimation*
**

Power calculations are based on serum TPO-Ab concentrations and LT4 dosage. Standard deviations used for power calculations were extracted from unpublished data in a study population of approximately 200 AIT patients from Copenhagen and Odense University Hospitals receiving LT4 treatment [14].

#### **
*Serum TPO-Ab concentration*
**

While a previous study has linked TPO-Ab positivity in hypothyroid patients to impaired HRQL [20], we have not found conclusive evidence in the literature that the level of serum TPO-Ab among participants in this trial, that is, AIT patients with serum TPO-Ab concentration ≥100 IU/ml, has clinical implications. The power estimate is based on a design with three repeated measurements having a compound symmetry covariance structure, with a standard deviation (σ level) of 535 IU/ml (unpublished data) [14], a correlation between observations on the same participant of 0.50, and a type I error probability (two-sided α level) of 0.05. Under these circumstances, a difference in serum TPO-Ab levels of 138 IU/ml between the experimental and control group can be identified with 80% power. We find the power of the trial to assess effect on serum TPO-Ab concentrations acceptable.

#### **
*LT4 dosage*
**

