In this trial, a difference in LT4 dosage of 25 μg/day between the experimental and control group following intervention should be detected, since 25 μg/day is a minimal dosage adjustment readily made by clinicians, when patients are treated with the most common LT4 formulation (Eltroxin) on the Danish market. The power estimate is based on a design with five repeated measurements having a compound symmetry covariance structure, with a standard deviation (σ level) of 81 μg/day (unpublished data) [14], a correlation between observations on the same participant of 0.50, and a type I error probability (two-sided α level) of 0.05. Under these circumstances, the probability (power) of finding a true difference in LT4 dosage of 25 μg/day between the experimental and control group following intervention is 92%, which we find acceptable.

#### **
*Expected participant recruitment*
**

The patient uptake areas for the participating clinical trial sites comprise a total of 910,000 persons (Rigshospitalet: 70,000; Odense University Hospital: 350,000; Bispebjerg Hospital: 270,000; Hospital of Southwest Denmark (Esbjerg): 220,000).

Previous studies report an incidence of 40 per 100,000 per year of spontaneous (presumed autoimmune) hypothyroidism after the implementation of iodine fortification in Denmark [5,6]. This corresponds to 364 patients per year in the given uptake area. A considerable proportion of hypothyroid patients are treated in the primary care sector, and will neither be referred to nor followed at a participating clinical trial site. Assuming an inclusion of 30% of the annual incident patients, we will be able to include 109 participants per year or nine participants per month. Half of the 472 participants will be included from the incident (LT4 treatment <3 months) group, and this is expected to take 24 to 26 months. In addition to this, established patients (LT4 treatment ≥ 3 months) with autoimmune thyroiditis are eligible for inclusion. The prevalence of diagnosed and treated hypothyroidism was 1% in a previous iodine fortification program (DanThyr) with a population of 4,073 men and women. 83% of hypothyroid patients had serum-TPO-Ab above 200 IU/ml [5]. An estimated AIT prevalence of 1% among adults in our patient uptake area will be approximately 10,000 individuals. We expect to recruit 236 participants from the prevalent patient group within the 24 to 26 month recruitment period of the incident patients.

#### **
*Data analyses*
**

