Analyses will be performed using SAS (SAS Institute Inc. ©, Cary, NC, USA), version 9.3 or later. All analyses will be intention-to-treat analyses performed blinded with the two intervention groups concealed as, for example, ‘A’ and ‘B’. Significance tests will be at the 5% level and two-sided. Table 2 shows, for each outcome, its priority, when it will be measured, the mathematical type of measure, and the analytical procedure to be used when analyzing the outcome values. The analytical procedures and handling of missing values are described next.

**Table 2 T2:** Outcome measures

**Outcome (priority)**	**Times of measurements**	**Mathematical type of quantity (analytical category)**
ThyPRO composite scale score (P)	Time sequence of six measurements^a^	Numerical (1 + 2)
ThyPRO hypothyroid symptoms (S)	Time sequence of six measurements^a^	Numerical (1 + 2)
ThyPRO goitre symptoms (S)	Time sequence of six measurements^a^	Numerical (1 + 2)
LT4 dosage (S)	Time sequence of four measurements^b^	Numerical (1 + 2)
Serum TPO-Ab (S)	Time sequence of four measurements^b^	Numerical (1 + 2)
Serum FT3/FT4 Ratio (S)	Time sequence of four measurements^b^	Numerical (1 + 2)
Plasma selenium (S)	Time sequence of four measurements^b^	Numerical (1 + 2)
Biomarkers of immunology and oxidative stress (S)	Time sequence of four measurements^b^	Numerical (1 + 2)
Adverse reactions (S)	End of trial	Rate (3)
Serious adverse events (S)	End of trial	Rate (3)

Outcomes with priorities, times of measurement and mathematical types of quantity with analytical categories. P, primary outcome measure; S, secondary outcome measure. Analytical categories 1 to 3 are defined in the main text. ^a^, includes five measurements relative to the reference time (6 weeks, 3 months, 6 months, 12 months and 18 months after randomization); ^b^, includes three measurements relative to the reference time (3 months, 12 months and 18 months after randomization).

#### **
*Analytical procedures*
**

Depending on the specific analytical category of each outcome measure, one or two of three types of regression analyses will be applied (Table 2).

#### **
*Analytical categories*
**

*Type 1* includes a continuous outcome measure (*y*) measured 3 to 6 times at 6 weeks, 3, 6, 12 or 18 months after randomization. It is viewed as a linear function of time (*t*). The model is:

*y* = *a* + *b***I* + *c***t* + *d***I***t*

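### The secondary power figures (138 IU/ml for TPO-Ab, 92% for LT4 dosage) do not follow from their stated repeated-measures designs, and LT4 dosage is not scheduled five times

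*Protocol article*

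**What the plan says.** All the power statements are in the protocol article under Statistical analyses.

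- **Primary outcome.** The target is a difference of "four points on the 0 to 100 ThyPRO composite scale", with SD 20, correlation 0.50, 80% power, two-sided 5% and five compound-symmetric measurements. The conclusion is that "a sample size of 236 experimental participants and 236 control participants is required".
- **Serum TPO-Ab.** With three compound-symmetric measurements, SD 535 IU/ml and correlation 0.50, "a difference in serum TPO-Ab levels of 138 IU/ml between the experimental and control group can be identified with 80% power".
- **LT4 dosage.** "The power estimate is based on a design with five repeated measurements having a compound symmetry covariance structure, with a standard deviation" of 81 μg/day, again with correlation 0.50. The power for a true difference of 25 μg/day "between the experimental and control group following intervention is 92"%.

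The protocol calls the power acceptable for both secondary outcomes.

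The schedule is in two places. Table 1 lists LT4 dosage and TPO-Ab at baseline, 3, 12 and 18 months. Table 2 gives each a sequence of four values, and its footnote b says that this "includes three measurements relative to the reference time (3 months, 12 months and 18 months after randomization"). Only ThyPRO has five times after randomization (footnote a).

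**The concern.** Three paragraphs describe the same kind of calculation, with the same covariance structure and the same correlation. The primary result shows that averaging over visits earned a clear reduction in sample size. The two secondary results show no such reduction, although their paragraphs claim three and five measurements. In addition, TPO-Ab and LT4 dosage are recorded at the same visits, yet one power statement counts three measurements and the other five.

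These figures tell a reader which TPO-Ab and LT4 effects the trial can detect, and they are the protocol's ground for accepting the secondary power. If TPO-Ab shows no effect, a reader will take 138 IU/ml as the detectable difference. The design described in that paragraph would support a smaller one.

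**Working it through.** **Inputs.** There are 236 participants per arm (primary sample size paragraph), and "the allocation ratio of intervention and control will be 1:1" (Randomization). "Significance tests will be at the 5% level and two-sided" (Data analyses). SDs, correlation 0.50 and numbers of measurements are those in the three paragraphs above. The secondary paragraphs do not repeat the number per arm, so 236 is assumed. No dropout is allowed for, as the Discussion says of the sample size.

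**Formulas.** For the mean of m compound-symmetric measurements with correlation 0.50, the variance relative to one measurement is

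f = (1 + (m − 1) × 0.5) / m

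so f = 1 (m = 1), 0.75 (m = 2), 0.667 (m = 3), 0.625 (m = 4) and 0.60 (m = 5). With 1.96 + 0.8416 = 2.8016:

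- n per arm = 2 × 2.8016² × SD² × f / difference²
- detectable difference at 80% power = 2.8016 × SD × √(2f/236)
- power = Φ(difference / (SD × √(2f/236)) − 1.96)

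**Step 1: the primary figure reproduces.** With m = 5, n = 2 × 7.849 × 400 × 0.60 / 16 = 235.5, so 236 per arm as stated. A single measurement would need 393. This identifies the method that gives the primary number.

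**Step 2: TPO-Ab.** For f = 1, the detectable difference is 2.8016 × 535 × √(2/236) = 137.98 IU/ml. For the stated m = 3, it is 137.98 × √0.667 = 112.7 IU/ml.

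**Step 3: LT4 dosage.** For f = 1, 25 / (81 × √(2/236)) = 3.353, and Φ(3.353 − 1.96) = 91.8%. For the stated m = 5, 3.353 / √0.60 = 4.328, and Φ(4.328 − 1.96) = 99.1%.

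| Measurements averaged | f | TPO-Ab difference at 80% power | Power at 138 IU/ml | LT4 power for 25 μg/day |
|---|---|---|---|---|
| 1 | 1.000 | **138.0** | 80.0% | **91.8%** |
| 2 | 0.750 | 119.5 | 89.9% | 97.2% |
| 3 | 0.667 | 112.7 | 93.0% | 98.4% |
| 4 | 0.625 | 109.1 | 94.3% | 98.9% |
| 5 | 0.600 | 106.9 | 95.1% | 99.1% |

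Only the first row matches the printed figures.

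**Step 4: other contrasts.**

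- *Change from baseline to one visit.* At correlation 0.50 the relative variance is 2 × (1 − 0.5) = 1, so this also gives 138.0 IU/ml and 91.8%.
- *Linear trend.* Over three equally spaced measurements f is again 1, which yields 138 for TPO-Ab. Over five equally spaced measurements it gives 96.3% for LT4, not 92%.
- *One-sided test, one measurement.* 122.5 IU/ml and 95.6%.
- *Baseline as covariate.* At most 119.5 IU/ml and at least 97.2%.

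None of the contrasts tried that uses all the stated measurements (three for TPO-Ab, five for LT4) gives both printed figures.

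**Step 5: the LT4 count.** Table 1 has four LT4 entries. Table 2 has four, of which three come after randomization. Neither with nor without baseline does the count reach five.

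**The case against.** The strongest defence is that a different contrast was intended. The secondary paragraphs never say that visits are averaged. The LT4 target is a difference "between the experimental and control group following intervention is 92"% likely to be found, and the wording can be read as an end-of-treatment comparison. In a repeated-measures model with complete data, an unadjusted group difference at one visit has single-measurement variance however many visits there are. Table 2 also assigns both outcomes the Type 2 analysis of a single value, alongside the Type 1 longitudinal model. On that reading 138 and 92% are right, and the fault is an unnamed contrast.

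This stands in part. A reader might infer that the authors ran a single-measurement calculation and mislabelled it. The documents do not support that as fact, since a change score at correlation 0.50 gives the same numbers. But the defence does not rescue the text: if the contrast is a single visit, the repeated-measures design in each paragraph does no work.

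A second objection concerns the replacement. The Discussion says that the 12-month period yields five measurements, yet ThyPRO has only four post-baseline times up to month 12, so that count includes baseline. Counted the same way, the three TPO-Ab measurements are baseline, 3 and 12 months, and 113 IU/ml, which averages three values, would not be the treatment contrast. This stands. A reader might take 119 IU/ml and 97% as the correct pair, but the protocol nowhere specifies an average of the 3- and 12-month visits, and footnote b of Table 2 includes month 18. The sponsor has to choose.

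Finally, the error is conservative: under every averaging variant the power exceeds the stated figure. That limits the consequence but does not make the statements correct.

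**Conclusion.** The point holds as a mismatch between stated design and stated result. Under the method that reproduces 236 per arm, three measurements give a detectable TPO-Ab difference of 112.7 IU/ml, about 18% below the printed 138 (1 − 112.7/137.98). At 138 IU/ml that design has 93% power. Five measurements give 99.1% for LT4, not 92%. The LT4 count of five contradicts Tables 1 and 2 whatever formula is used.

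The recomputed figures assume 236 per arm with complete data, the stated SDs and correlation, a normal approximation, and a mean-over-visits contrast. A t-based calculation changes little (LT4 91.7% for one measurement, 99.1% for five).

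A reader might go further and conclude that the trial is underpowered for these outcomes or wrongly sized. The documents do not support this: the primary calculation reproduces, the secondary figures understate power, and the judgement that secondary power is acceptable survives under the averaging variants.

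**What to change.** 1. In the LT4 dosage paragraph, replace five with the scheduled number of measurements, and say whether baseline is counted.
2. Then do one of the following for both outcomes:
   - name the measurements that the analysis will use and restate the figures for them: about 113 IU/ml and 98% for the three post-randomization visits, or about 119 IU/ml and 97% for 3 and 12 months only; or
   - state that 138 IU/ml and 92% refer to a single-visit comparison, name the visit, and remove the repeated-measures description.

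The cost is a text correction in two paragraphs. Sample size, schedule and conduct do not change.

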**Methods/Design:**

The CATALYST trial is an investigator-initiated randomized, blinded, multicentre clinical trial of selenium supplementation versus placebo in patients with chronic autoimmune thyroiditis. Inclusion criteria: age ≥18 years; serum thyroid peroxidase antibody level ≥100 IU/ml within the previous 12 months; treatment with levothyroxine and written informed consent. Exclusion criteria: previous diagnosis of toxic nodular goitre, Graves’ hyperthyroidism, postpartum thyroiditis, Graves’ orbitopathy; previous antithyroid drug treatment, radioiodine therapy or thyroid surgery; immune-modulatory or other medication affecting thyroid function; pregnancy, planned pregnancy or breastfeeding; allergy towards any intervention or placebo component; intake of selenium supplementation >55 μg/day; inability to read or understand Danish or lack of informed consent. The trial will include 2 × 236 participants. The experimental intervention and control groups will receive 200 μg selenium-enriched yeast or matching placebo tablets daily for 12 months. The experimental supplement will be SelenoPrecise^®^. The primary outcome is thyroid-related quality of life assessed by the Thyroid Patient-Reported Outcome (ThyPRO) questionnaire. Secondary outcomes include serum thyroid peroxidase antibody concentration; serum triiodothyronine/thyroxine ratio; levothyroxine dosage; adverse reactions and serious adverse reactions and events.

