### Outcomes

Data will be collected for outcome assessment at six specified times during the trial (Table 1).

**Table 1 T1:** Timing of data collection

**Variable**	**Inclusion baseline**	**Follow-up 6 weeks ± 1 week**	**Follow-up 3 months ± 2 weeks**	**Follow-up 6 months ± 2 weeks**	**Follow-up 12 months ± 2 weeks**	**Follow-up 18 months ± 2 weeks**
Visit	*x*		*x*		*x*	*x*
Weight	*x*_ *v* _		*x*_ *v* _		*x*_ *v* _	*x*_ *v* _
Medical treatment	*x*_ *v* _		*x*_ *v* _		*x*_ *v* _	*x*_ *v* _
ThyPRO	*x*_ *r* _	*x*_ *r* _	*x*_ *r* _	*x*_ *r* _	*x*_ *r* _	*x*_ *r* _
TSH, FT4, FT3	*x*_ *s* _		*x*_ *s* _		*x*_ *s* _	*x*_ *s* _
TPO-Ab	*x*_ *s* _		*x*_ *s* _		*x*_ *s* _	*x*_ *s,* _
LT4 dosage	*x*_ *v* _		*x*_ *v* _		*x*_ *v* _	*x*_ *v* _
Immunological and oxidative stress biomarkers	*x*_ *s* _		*x*_ *s* _		*x*_ *s* _	*x*_ *s* _
Selenium	*x*_ *s* _		*x*_ *s* _		*x*_ *s* _	*x*_ *s* _
Creatinine/iodine ratio in spot urine	*x*_ *s* _					
Tablet count			*x*_ *v* _		*x*_ *v* _	
Consumption of additional selenium	*x*_ *v* _		*x*_ *v* _		*x*_ *v* _	*x*_ *v* _
Adverse reactions			*x*_ *v* _		*x*_ *v* _	*x*_ *v* _
Serious adverse reactions and events (SARs, SUSARs and SAEs)						*x*_ *p* _

All assessments must be made at the time points specified above. If not possible at the specified time, the assessment shall still be conducted, and the time of assessment shall be noted in the specified electronic case report form (eCRF). *x*_
*v*
_, analyzed via data obtained in eCRFs at trial visits, administered through the trial data management system (TDMS); *x*_
*r*
_, analyzed via patient-reported outcomes, administered through the TDMS; *x*_
*s*
_, analyzed in blood or urine samples obtained at trial visits; *x*_
*p*
_, analyzed via public national registries at the end of the trial.

#### **
*Primary outcome*
**

Improved thyroid-related quality of life during the 12 months intervention after randomization, as measured by one composite score from the ThyPRO questionnaire [49].

#### **
*Secondary outcomes*
**

Secondary outcome assessment is specified in Table 1. Forkhead Box P3 mRNA will be measured as an immunological biomarker, and urinary 8-oxo-2'-deoxyguanosine and 8-oxoguanine will be measured as oxidative stress biomarkers.

#### **
*Assessment of adverse reactions and events*
**

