Depending on the mean value structure in the two groups, this model may be enhanced to include a second- or third-degree polynomial. *I* is the intervention indicator, and *a*, *b*, *c* and *d* are the coefficients of the regression equation. A mixed model with repeated measures will be used. An unstructured covariance matrix will be used. In the case of lack of convergence, the following covariance structures will be tried in the specified order: the spatial power law and the compound symmetric.

*Type 2* includes a single continuous outcome measure. The general linear univariate model will be used. As a sensitivity analysis, a nonparametric test (Mann Whitney) will be conducted and the result discussed.

*Type 3* includes a count of events within a specified period of counting as outcome measure. The generalized linear model will be used with the Poisson distribution, link = log and log (period) as offset. As a sensitivity analysis a nonparametric test (Mann Whitney) is conducted to compare the distributions of rates between the groups and the result discussed.

#### **
*Missing values*
**

If the distributions of the primary outcome measure differ significantly between the two intervention groups, multiple imputations (MI) will be used to replace missing data with substituted values using SAS version 9.3 or later. In the MI analysis, the model variables and additional variables significantly related to the variables with missing values of these variables will be used. Ten imputed data sets will be produced.

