## Discussion

The data available from previous trials warrant further investigation, since a benefit from selenium supplementation is still unproven in patients with AIT. In previous trials of intervention with selenium in patients with AIT, effect on serum TPO-Ab concentration has been the primary outcome. Intervention durations of 3, 6, 9, and 12 months using different selenium formulations have shown positive effects on serum TPO-Ab concentrations. This trial will be the largest yet, with 472 participants, and the first to measure changes in quality of life, by ThyPRO, as the primary outcome. The sample size estimate does not take dropouts or off-trial use of selenium supplements into account. Plasma selenium concentrations will be measured to assess selenium intake during the trial. Importantly, utilizing the ThyPRO questionnaire will enable us to determine how selenium supplementation may affect specific aspects of thyroid-related quality of life in AIT patients. In assessing quality of life, the effect of levothyroxine alone will be taken into account by adjusting for TSH levels. Choosing a 12-month intervention period allows for a time sequence of five measurements. The 6-month postintervention follow-up period was added to assess sustained effects. This trial will also look into selenium’s mechanisms of action in AIT, by measuring biomarkers of immunological activity, and will be the first to evaluate whether selenium supplementation affects LT4 dosage. Dosage reduction is of clinical interest and discontinuation of LT4 would be of direct clinical relevance. An effect of selenium supplementation on LT4 dosage is conceivable, owing to upregulation of selenoproteins involved in thyroid hormone synthesis or thyrocyte protection.

Participants will be stratified for LT4 treatment duration of more or less than three months, corresponding to newly diagnosed and established patients, respectively. Participants in the newly diagnosed patient group will respond to LT4 treatment *per se*, in terms of restoration of euthyroidism, while the established patient group will not experience major fluctuation in the thyroid hormone levels during the study period. The stratification also allows an investigation of whether the newly diagnosed and established patient groups respond differently to selenium supplementation. This investigation will, however, be strictly exploratory, as it is likely to be underpowered.

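### The primary outcome covers the 12 months on tablets, but the primary model also takes in the 18-month ThyPRO score, measured six months after the tablets stop

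*Protocol article*

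**What the plan says.** Outcomes, Primary outcome: "Improved thyroid-related quality of life during the 12 months intervention after randomization, as measured by one composite score from the ThyPRO questionnaire". The sample size section repeats that window ("The primary outcome is thyroid-related quality of life during 12 months"), the Objectives use it as well, and the abstract gives the treatment as selenium "or matching placebo tablets daily for 12 months".

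Table 2 assigns the primary composite six measurements and analytical categories 1 and 2. Footnote a explains that the sequence "includes five measurements relative to the reference time (6 weeks, 3 months, 6 months, 12 months and 18 months after randomization". The Type 1 description says the outcome is "measured 3 to 6 times at 6 weeks, 3, 6, 12 or 18 months after randomization" and models it as a straight line in time with an intervention-by-time term, y = a + b·I + c·t + d·I·t. It adds that "this model may be enhanced to include a second- or third-degree polynomial", depending on the mean structure in the two groups. Covariance is unstructured first, then spatial power, then compound symmetric.

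The Discussion gives the last visit a different purpose: "The 6-month postintervention follow-up period was added to assess sustained effects". It also ties a sequence of five measurements to the 12-month intervention period. No text removes 18 months from the primary analysis, and none says which coefficient or contrast is the primary test.

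**The concern.** The question asked and the data used to answer it cover different periods. A score taken six months after the last tablet says nothing direct about quality of life during treatment, yet it enters the same regression as the on-treatment scores. In a model linear in time it is also the point furthest from the mean time, so it pulls hardest on the slope. If a benefit fades once tablets stop, the primary estimate shrinks although the on-treatment benefit was real.

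The count of five measurements is also unstable. Footnote a reaches five by including 18 months and leaving out baseline. The Discussion reaches five within 12 months, which by Table 1 means baseline, 6 weeks, 3, 6 and 12 months. The sample size uses five without saying which.

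**Working it through.** **Inputs from the article.** Difference 4 points, SD 20, within-participant correlation 0.50, five repeated measures, compound symmetry, two-sided 5%, 80% power, 236 per group. **Assumed:** the effect remaining at 18 months (4, 2 or 0 points) and the shape of the effect over time. The article gives neither.

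**1. The plan's own figure.** The variance of a participant's mean over m measures is 20² × (1 + (m − 1) × 0.5)/m. For m = 5 this is 400 × 0.6 = 240 (SD 15.49). Then n = 2 × (1.960 + 0.842)² × 240/4² = 235.5, so 236 per group, with power 80.1%. The stated size is reproduced as a comparison of five-visit means in which every visit carries the full 4 points.

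**2. Average over the five post-baseline visits.** With 4 points at 6 weeks, 3, 6 and 12 months and r points at 18 months, the average effect is (4 × 4 + r)/5.

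| r at 18 months | Average effect | Power at 236 per group | n per group for 80% |
|---|---|---|---|
| 4 | 4.0 | 80.1% | 236 |
| 2 | 3.6 | 71.4% | 291 |
| 0 | 3.2 | 61.2% | 368 |

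If the five are baseline plus the four on-treatment visits, baseline carries no effect, and a plain five-visit mean again gives 16/5 = 3.2.

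**3. Linear model.** Six measurements must include baseline, because only five later times are listed. With balanced data and compound symmetry, the group difference is fitted by ordinary least squares. Taking 6 weeks as 1.5 months, the times are 0, 1.5, 3, 6, 12 and 18. Their mean is 40.5/6 = 6.75, and the sum of squares about it is 515.25 − 273.375 = 241.875. The 18-month visit contributes 11.25² = 126.56, which is 52%.

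- *Step* (0, 4, 4, 4, 4, 0): mean effect 16/6 = 2.667; cross-product 90 − 40.5 × 2.667 = −18; slope −18/241.875 = −0.074 per month; fitted at 12 months 2.667 − 0.074 × 5.25 = 2.28.
- *Ramp* (0, 0.5, 1, 2, 4, 0): mean 7.5/6 = 1.25; cross-product 63.75 − 50.625 = 13.125; slope 0.054; fitted at 12 months 1.25 + 0.054 × 5.25 = 1.53.

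The same steps with 2 or 4 points at 18 months give:

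| r | Step: slope per month, fitted at 12 months | Ramp: slope per month, fitted at 12 months |
|---|---|---|
| 4 | 0.112, 3.92 | 0.240, 3.18 |
| 2 | 0.019, 3.10 | 0.147, 2.36 |
| 0 | −0.074, 2.28 | 0.054, 1.53 |

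Profiles that reach 4 points by 3 or by 6 months lie between these. With data to 12 months only, the step gives slope 0.200 and 4.7 at 12 months, and the ramp gives 0.333 and 4.0.

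**4. Polynomial, r = 0.** Fitted 12-month difference: step 4.18 (quadratic) and 3.59 (cubic); ramp 3.00 and 3.93.

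**5. Cost of stopping at 12 months.** For the unadjusted mean of four on-treatment visits, the variance is 400 × 2.5/4 = 250; power is 78.5% at 236 per group, and 80% needs 246. With baseline as covariate at correlation 0.50, the variance is 400 × (0.625 − 0.25) = 150; power is 94.4%, and 80% needs 148.

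**The case against.** The best defence is that Table 2 is only a measurement schedule and that the intent is clear elsewhere: the Objectives, the outcome definition and the sample size all refer to the 12-month intervention, and the Discussion gives 18 months its own purpose. The intent is indeed clear, but the schedule reading fails because the Type 1 model text itself names 18 months. Type 2, a single-measure analysis, is also listed for the primary outcome, but without a time point, so it does not settle the matter. An analysis plan that is not shown might name the contrast; it would then have to depart from what is printed here.

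Four objections to the size of the effect do stand.
- The polynomial recovers most of the lost 12-month difference in the zero-residual examples. It is optional and chosen from the observed means, so it is not a pre-specified safeguard.
- The 52% and the slopes assume compound symmetry, the plan's last fallback. Under an unstructured covariance the weights will differ.
- Part of the misfit belongs to the straight line and not to month 18: without that visit the step profile still gives 4.7 against a true 4.
- If the effect persists in full, the average is not diluted at all.

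A reader might infer that the trial's result could be reversed, or that the trial cannot answer its primary question. The article does not support this. The time-averaged difference stays positive throughout. With baseline in the model, as six measurements imply, the interaction coefficient turns negative only with early onset and near-total loss by 18 months. Fitted to post-baseline visits alone, the step profile is already negative at half retention (−0.106 per month). In neither case is that coefficient named as the primary test.

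A reader might also carry the point over to the footnote b outcomes. No 12-month window is stated for them, so there is no contradiction to correct.

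**Conclusion.** The mismatch is in the text and holds. An outcome defined as "Improved thyroid-related quality of life during the 12 months intervention after randomization" is assigned an analysis that includes an off-treatment score, and the five measurements are counted in two ways. This can bias the primary estimate, so it should be settled before analysis.

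The size is conditional. It ranges from no dilution of the visit average at full retention to a fifth (4.0 to 3.2 points, power from about 80% to 61%) at complete loss. The linear model's 12-month difference is affected even at full retention (3.2 to 3.9), and more at half (2.4 to 3.1) and at none (1.5 to 2.3). These linear figures assume 4 points at 12 months, compound symmetry, complete data and no polynomial term.

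**What to change.** State that the primary contrast uses data up to 12 months (baseline, 6 weeks, 3, 6 and 12 months) and name one contrast as the primary test. Categorical visits with baseline adjustment are preferable, because dropping 18 months while keeping a straight line leaves the misfit shown above. Report 18 months as a separate sustained-effect contrast. Correct Table 2 footnote a and the Type 1 text accordingly, and make the five measurements mean the same visits in the sample size section, Table 2 and the Discussion. Applying the same separation to the footnote b outcomes is optional.

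The cost is a change of wording, with no extra participants or data. An unadjusted mean of the four on-treatment visits loses about 1.6 percentage points of power (78.5% against 80.1% at 236 per group). Baseline adjustment at the plan's own correlation more than recovers that.
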